Coenzyme Q10 (CoQ10) is a fat-soluble antioxidant occurring naturally in the inner membrane of the cell's mitochondria. It plays an essential role as a diffusible electron carrier in the electron transport chain (18, 19). CoQ10 has two forms: the oxidized form and the reduced, active form. This reduced form is widely used in the adjunctive treatment of cardiovascular diseases, nutritional health products, and food additives (20). Notably, CoQ10 plays a key role in myocardial hypoxia, significantly boosting heart health. In patients with myocardial ischemia and hypoxia, ubiquinol, the reduced-form supplement (19, 21, 22), increases aerobic metabolism efficiency and raises the anaerobic threshold. This signifies a lesser need to resort to anaerobic energy production at the same workload (19, 21, 22). Ubiquinol is necessary for the body to produce energy; however, its content in the organism decreases with age and may lead to diseases (23). The lack of ubiquinol causes less efficiency, quick fatigue, and weakened cellular protection ability against oxidative stress (19). These clinical trials implied that ubiquinol could reverse the loss of physical performance ability both at high altitudes and at return to sea level.

We designed this double-blinded, placebo-controlled clinical trial to investigate the hypothesis that ubiquinol supplementation could improve cardiorespiratory fitness, which may be impaired during high-altitude acclimatization and de-acclimatization. This novel Shigatse CARdiorespiratory Fitness (SCARF) study has the potential to identify whether ubiquinol supplementation may rescue the loss of exercise capacity and impaired cardiorespiratory fitness during acute hypoxia and the reoxygenation process. We believe this is the first study that prospectively and accurately evaluates cardiorespiratory fitness during high-altitude acclimatization and de-acclimatization. We also explore the effect of ubiquinol on blood metabolic substrate and automatic nervous function to illustrate the possible beneficial mechanisms further.

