### Study design

2.6.

Figure 1 shows the flow chart of this study. Participants will take ubiquinol orally with a dose of 200 mg daily or a placebo for 14 days before departure. Physical examination, symptoms related to high-altitude acclimatization and de-acclimatization, cardiorespiratory exercise test, laboratory test, and any possible adverse reaction of ubiquinol and exercise will be collected at baseline detection and each visit. During the 14 days of the medication, only participants who did not experience these adverse effects would go to the high altitude as scheduled. It would help us identify related symptoms at high altitudes due to hypoxia rather than adverse events of ubiquinol. The laboratory and exercise tests will be conducted separately on the last three days of the 14 days. Subsequently, they will board a flight to Shigatse (high altitude area, 3,900 m) in 3 h. After arriving at Shigatse, the AMS symptom self-administered questionnaires and adverse reactions of ubiquinol will be followed up daily, and the other prior programs will be carried out on the third day. The subjects will then be flown back to a low altitude after staying for 7 days at a high altitude and scored for HADAS, followed by other prior programs at a low altitude on the 7th day after return. The last visit will be set in the sixth month of this study, which has not yet been conducted. Laboratory tests include a blood routine test of 19 parameters commonly used in the clinic and a serological test of 19 circulating indicators, including glucose, total cholesterol, triglyceride, low-density lipoprotein cholesterol, high-density lipoprotein cholesterol, lactate, non-esterified fatty acid, norepinephrine, epinephrine, plasma renin activity, angiotensin Ⅱ, angiotensin-converting enzyme 2, neuropeptide Y, atrial natriuretic peptide, lactate dehydrogenase, insulin, glucocorticoid, adiponectin, and leptin.

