#### Statistical considerations

2.11.2.

Continuous variables will be expressed as means ± standard deviations (SD) or as median (interquartile spacing), and categorical variables as *n* (%) according to the Shapiro–Wilk test. Generalized estimating equations (GEE) with an exchangeable working correlation will be employed. Treatment, altitude, and the treatment multiplied by altitude interaction will be considered independent variables under mixed models. At each altitude, a comparative analysis will be carried out between two groups (ubiquinol group and placebo group), and the least significant difference method will be performed to adjust within-altitude differences for multiple comparisons. Correlation analyses will be performed using Pearson correlation for continuous variables, and Spearman Rank tests will be used between categorical variables. In addition, subgroups will be defined by age for analysis since it is known that ubiquinol levels decrease with age (23). Two-sided tests with *p*-values less than 0.05 will be considered statistically significant. IBM SPSS Statistics software for Windows (version 26, IBM, Armonk, NY, United States) will be used for statistical analyses.

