## Discussion

3.

To the best of our knowledge, this study is the first to evaluate cardiorespiratory fitness prospectively and accurately during the high-altitude acclimatization and de-acclimatization process. Moreover, it is a double-blinded, placebo-controlled trial to explore the effects of ubiquinol on cardiorespiratory fitness during acclimatization and de-acclimatization. The clinical trial design depicts cardiorespiratory fitness characteristics at high-altitude acclimatization and de-acclimatization and is designed to reveal cardiovascular and respiratory function restoration during de-acclimatization. In addition, we determine whether ubiquinol supplementation is beneficial for endurance exercise capacity at a high altitude and helps with better adaptation to acute hypoxia exposure. Furthermore, we explore the relationship between the circulating substances and physical performance capacity at high altitudes to be able to account for the possible mechanisms.

The exploration of medicines for high-altitude acclimatization has been underway for decades. A few drugs, such as acetazolamide and *Rhodiola rosea*, have been recommended to promote acclimatization (16, 44, 45). However, limited research focused on the process of de-acclimatization and related symptoms. Thus, in this study, we recruited healthy Han Chinese from Chongqing to assess the possible effect of ubiquinol on cardiorespiratory fitness, AMS, and HADAS symptoms. A previous trial has reported that CoQ10 supplementation with a dose of 90 mg for 6 weeks orally could improve VO_2_max, aerobic, and anaerobic thresholds, indicating the increase of cardiorespiratory fitness of endurance athletes (21). In addition, studies demonstrated that CoQ10 deficiency was positively associated with fatigue, whereas serum CoQ10 levels were inversely correlated with fatigue severity (46, 47). In addition, another meta-regression also confirmed that a daily dose of CoQ10 was associated with fatigue reduction (48). Therefore, we suppose that ubiquinol supplementation at high altitudes may alleviate AMS and HADAS-related symptoms and maintain cardiorespiratory fitness.

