Cardiorespiratory fitness reflects the comprehensive ability of the body to transport and utilize oxygen and embodies the overall function of the respiratory and cardiovascular systems (49, 50). VO_2_max is the gold standard for assessing cardiorespiratory fitness and an independent predictor of cardiovascular events and mortality (51–53). Previous studies have indicated that VO_2_max decreases linearly by approximately 8% for every 1,000 m of additional elevation above 700 m, while it descends in an accelerated curve over 6,300 m, suggesting that cardiorespiratory function is impaired at high altitudes (54). However, there is limited information on cardiorespiratory fitness changes during de-acclimatization from a high altitude in healthy individuals, and the underlying mechanisms remain to be elucidated. Thus, in this study, we try to illuminate the possible mechanism by circulating markers of metabolism and the autonomic nervous system (55).

This study has some limitations. First, although this is not a small clinical trial in the CPET trial at a high altitude, this study is limited by a small sample size (*n* = 41) and short follow-up (on days 17 and 28, respectively). Therefore, it is troublesome to implement hierarchical analysis, and these preliminary results need to be confirmed in a large cohort. Second, long-term follow-up may be more meaningful in evaluating ubiquinol supplements on cardiorespiratory fitness.

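### Unadjusted Pearson correlations of blood markers with fitness at altitude cannot by themselves point to a hypoxia or ubiquinol mechanism, and no error control is stated for them

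*Protocol article*

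**What the plan says.** All references are to the protocol article.

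- **Method.** Section 2.11.2 (Statistical considerations): "Correlation analyses will be performed using Pearson correlation for continuous variables". This is the only method given there for relating two continuous variables to each other. The variables, the visit, and the choice between levels and changes are not named.
- **Decision rule.** The same section says that p-values "less than 0.05 will be considered statistically significant", two-sided.
- **Multiplicity.** The only procedure named is for group comparisons: "the least significant difference method will be performed to adjust within-altitude differences for multiple comparisons". Nothing is stated for the correlations.
- **Purpose.** Section 3 (Discussion): "we explore the relationship between the circulating substances and physical performance capacity at high altitudes to be able to account for the possible mechanisms", and later "we try to illuminate the possible mechanism by circulating markers of metabolism and the autonomic nervous system".
- **A second route to mechanism.** Section 1 (Introduction): "We also explore the effect of ubiquinol on blood metabolic substrate and automatic nervous function to illustrate the possible beneficial mechanisms further". This is an effect of treatment on the markers, so a randomised comparison.
- **Data.** Section 2.6 lists "a serological test of 19 circulating indicators" and 19 blood-count parameters. Section 2.5 lists 14 exercise-test parameters. Table 1 schedules exercise test, blood count and serum markers on days 11, 17 and 28, and records age, sex, height and weight.

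**The concern.** The null hypothesis of a Pearson test is that, across people, the marker and the fitness measure are uncorrelated. Treatment arm does not enter it, and neither does the change from low altitude to high altitude. Anything that makes some people differ stably from others in both variables will make that null false, even if the marker plays no part in the response to hypoxia or to ubiquinol.

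Sex, age and body size are obvious candidates. Table 5 defines % predicted peak VO2 against a value predicted from those three characteristics, so raw peak VO2 is taken to depend on them. Table 2 admits adults with no upper age limit, and its only sex-related exclusion is pregnancy or nursing.

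The second problem is the number of possible tests, each read at 0.05. Between-person differences and chance findings could then be written up as pathways of acclimatization or of benefit from ubiquinol.

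**Working it through.** **Sample size available.** The article gives no figure for the correlation analysis. Section 2.3 gives 39 evaluable participants and 41 after a 5% allowance: 39 × 1.05 = 40.95, which rounds to 41, so the stated total is reproduced. (Dividing instead, 39/0.95 = 41.05, gives 42; the difference is immaterial here.) I use n = 39.

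**Threshold for significance.** |r| = t/√(n − 2 + t²), with t the two-sided 5% point on n − 2 degrees of freedom. This gives 0.316 at n = 39 and 0.308 at n = 41.

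**Chance alone.** The article does not name the pairs, so these are counts over full grids at one visit.
- Serum markers by exercise-test parameters: 19 × 14 = 266 pairs; 266 × 0.05 = 13.3 expected significant results if all are null.
- With the blood count added: 38 × 14 = 532 pairs; 532 × 0.05 = 26.6.
- Chance of at least one among 266 if the tests were independent: 1 − 0.95^266, above 0.9999.
- The variables within each set will be correlated, by an amount the article does not give. Simulated with assumed correlations of 0.2 among markers and 0.5 among exercise parameters, the chance is 0.999; with 0.3 and 0.7 it is 0.984; with 0.7 in both sets it is 0.87. The expected number stays at about 13.

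**Between-person differences, with sex as the example.** Take a marker and a fitness measure that are unrelated within each sex. Let p be the share of the minority sex, and d1 and d2 the sex differences in within-sex SD units. The induced correlation is the product, over the two variables, of d√(p(1−p)) / √(1 + d²p(1−p)). For p = 0.5 and d1 = d2 = 1, each factor is 0.5/√1.25 = 0.447, so r = 0.20.

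The article gives none of these inputs, so they are assumptions. Each cell shows the induced r and the share of 20,000 simulated trials (n = 39) with p<0.05:

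| p | d 0.5, 0.5 | d 1, 1 | d 1.5, 1 | d 1.5, 1.5 | d 2, 1.5 |
|---|---|---|---|---|---|
| 10% | 0.022; 5.3% | 0.083; 7.6% | 0.118; 11.2% | 0.168; 18.9% | 0.211; 26.7% |
| 25% | 0.045; 5.8% | 0.158; 16.7% | 0.216; 27.4% | 0.297; 48.8% | 0.357; 66.7% |
| 50% | 0.059; 6.5% | 0.200; 23.9% | 0.268; 40.0% | 0.360; 65.8% | 0.424; 82.9% |

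With sex partialled out, the rejection rate is 4.7% to 5.2% in every cell. Age and body size were not simulated.

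**What error control would do.** A Bonferroni limit over 266 pairs is 0.05/266 = 0.000188, which raises the critical |r| at n = 39 from 0.316 to 0.563. With one fitness measure and 19 markers, 19 × 0.05 = 0.95 false positives are expected without correction, and the Bonferroni critical |r| is 0.468.

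**The case against.** The strongest case against the point has five parts.

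1. *No test of every marker against every fitness measure is planned.* Section 2.11.2 names no pairs, and a Pearson correlation of change scores would fit its words. This stands: 266 is a ceiling for the serum markers at one visit. But the Discussion speaks of the relationship at high altitude, for which levels at that visit are the natural reading, and no other method is offered for it.
2. *Mechanism also has a randomised route.* This stands. The Introduction plans to study the effect of ubiquinol on the markers, and section 2.11.2 has treatment and treatment-by-altitude terms. Sex and body size do not systematically confound that contrast. A reader might infer that correlations are the only basis for mechanism; the article does not say so.
3. *The confounding may be small.* A reader might infer that sex and body size are bound to produce false mechanisms, or that a mechanism would be declared whatever the data. The article does not support either. It gives no sex mix, and the table runs from essentially no inflation to a very large one. The bias is also uneven: % predicted peak VO2 is already standardised for age, sex and body size, and metabolic equivalents for weight.
4. *The analysis is exploratory.* The markers are neither primary nor secondary outcomes, and the Discussion speaks of possible mechanisms and preliminary results. That lowers the stakes but does not make the test address mechanism.
5. *An article condenses the plan.* Covariates, pairs and error control may be set out elsewhere, and their absence alone would not be a finding. The point rests on what is stated: a plain correlation at 0.05, put to a mechanistic use.

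**Conclusion.** The point holds in a limited form. As written, the method tests association between people; it brings in neither arm nor change from low altitude, so a significant result cannot by itself indicate a hypoxia or ubiquinol mechanism. With no error control stated, testing the full serum grid at 0.05 would yield about 13 significant pairs out of 266 even if none were real. A shorter list would yield proportionately fewer.

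The effect of stable differences between people cannot be sized from the article. The range of about 5% to 83% for sex rests on assumed sex shares of 10% to 50% and assumed sex differences of 0.5 to 2 SD, and applies only to measures not already standardised. The primary comparison and the randomised comparison of markers are untouched. The change is worth making, but it concerns a supporting analysis.

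**What to change.** In section 2.11.2, for the mechanism question:

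- Replace the plain correlations with partial correlations or regressions relating marker and fitness, adjusted for treatment arm, sex, age and body mass. Preferably use within-person change, from day 11 to day 17 and from day 17 to day 28. Change scores remove stable differences between people and address what happens with altitude. Day 11 falls after dosing has begun, so these are changes with altitude, not changes from an untreated baseline.
- Name a short list of marker–fitness pairs, or apply a false-discovery-rate procedure across the set.
- State that any claim about a ubiquinol mechanism rests on the randomised comparison of markers between arms.
- Report the correlations as hypothesis-generating associations.

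The cost is a wording change and a little more analysis; Table 1 already schedules every variable needed. The downside is that change scores carry more measurement noise, adjusting for four covariates with about 39 people costs some precision, and fewer correlations will be nominally significant. The adjusted associations remain observational.

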**4. Participant requests for reasons other than above**

### Outcomes

2.5.

The primary outcome will be the cardiorespiratory fitness characteristics both at high-altitude acclimatization and de-acclimatization after ubiquinol supplementation. Specifically, the parameters including peak oxygen consumption (VO_2_), % predicted peak VO_2_, VO_2_ at the anaerobic threshold (AT), peak O_2_ pulse, metabolic equivalents, % maximum predicted heart rate, rate pressure product, VE/VCO_2_ slope, oxygen uptake efficiency slope, VO_2_/work rate slope, cardiac output, exercise ventilatory power, circulatory power, and dead space ventilation / tidal volume at these four visits will be collected for further analysis. A brief definition of these indicators is as follows: peak VO_2_, peak oxygen consumption during an incremental exercise protocol with or without a plateau; % predicted peak VO_2_, peak VO_2_ divided by predicted peak VO_2_; VO_2_ at AT, the value of VO_2_ at AT time; peak O_2_ pulse, the peak oxygen extracted with each beat of the heart; metabolic equivalents, the ratio of exercise metabolic rate to resting metabolic rate calculated as VO_2_/3.5 ml/min/kg; % maximum predicted heart rate, heart rate divided by maximum predicted heart rate; rate pressure product, the product of heart rate and systolic blood pressure; VE/VCO_2_ slope, from exercise onset to peak exercise by the slope of linear regression of VE and VCO_2_; oxygen uptake efficiency slope, slope of the regression line of VO_2_ vs. log_10_ VE; VO_2_/work rate slope, *Δ*VO_2_/*Δ*work rate during incremental exercise; cardiac output, the amount of blood the heart pumps per minute; exercise ventilatory power, the ratio between peak SBP and the VE/VCO_2_ slope; circulatory power, the product of CO and mean arterial BP; dead space ventilation / tidal volume, an estimate of the ventilation-perfusion ratio. In addition, the detailed definitions and calculation methods of these indicators are shown in Table 5.

**Table 5 T5:** The measurement approach for each CPET variable.

CPET fitness measure	Physiological significance	Measurement methodology

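### Section 2.11.2 fixes Pearson for every continuous variable and Spearman for categorical ones, at p<0.05 with no error control named: a minor, cheaply mended weakness in an exploratory analysis

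*Protocol article*

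**What the plan says.** All the relevant rules stand in one paragraph of the protocol article, section 2.11.2 (Statistical considerations).

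- **Correlation method:** "Correlation analyses will be performed using Pearson correlation for continuous variables, and Spearman Rank tests will be used between categorical variables".
- **Normality:** continuous variables are summarised by mean and SD "or as median (interquartile spacing"), the choice being made "according to the Shapiro–Wilk test". The test is tied to the descriptive summary only.
- **Threshold:** tests are two-sided, and p-"values less than 0.05 will be considered statistically significant". No exception is made for correlations.
- **Multiplicity:** "the least significant difference method will be performed to adjust within-altitude differences for multiple comparisons". Nothing is named for correlations.

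Section 2.5 (Outcomes) lists the exercise-test measures, ending with "circulatory power, and dead space ventilation / tidal volume at these four visits will be collected for further analysis". Section 2.6 (Study design) plans "a blood routine test of 19 parameters commonly used in the clinic and a serological test of 19 circulating indicators". The Discussion (section 3) describes the purpose as exploring how circulating substances relate to physical performance at high altitude, in search of possible mechanisms. No correlation is listed as a primary or secondary outcome.

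**The concern.** Three choices in this paragraph fit poorly.

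1. The plan foresees non-normal continuous variables and changes their descriptive summary, but not their correlation. A skewed marker is reported by its median and then correlated by a linear measure that a few large values can dominate.
2. A rank correlation needs ordered categories. It suits graded symptom scores (the Lake Louise items and the de-acclimatization grade in section 2.8 both run from 0 to 3). It has no meaning for a variable with three or more unordered categories, and the wording does not exclude such variables.
3. Many markers can be set against many exercise measures, each pair judged at 0.05. Some will look significant by chance, and a reader has no stated count of tests to judge them by.

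At stake is how far the exploratory, mechanistic part of the report can be trusted. The randomised comparisons are not involved.

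**Working it through.** The plan gives no figure of its own to reproduce, so the check has three parts.

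**1. Expected false positives**

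Inputs:
- Exercise-test measures: 14, counted from the list in section 2.5.
- Laboratory measures: 19 routine blood parameters + 19 serum indicators = 38 (section 2.6).
- Threshold: 0.05 (section 2.11.2).
- Number of pairs: not stated, so a range is shown.

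Formula: expected false positives = pairs × 0.05, assuming every null hypothesis is true. This expectation does not require independent tests.

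| Assumed set | Pairs | Expected false positives |
|---|---|---|
| Peak VO2 × 19 serum indicators | 19 | 19 × 0.05 = 0.95 |
| Peak VO2 × all 38 laboratory measures | 38 | 38 × 0.05 = 1.9 |
| 14 measures × 19 serum indicators | 266 | 266 × 0.05 = 13.3 |
| 14 measures × all 38 laboratory measures | 532 | 532 × 0.05 = 26.6 |

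The third row is closest to the Discussion, which speaks of circulating substances and performance at high altitude. For the smallest set, the chance of at least one false positive, if the tests were independent, is 1 − 0.95^19 = 0.62.

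**2. Does skewness inflate Pearson's false-positive rate?**

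This was simulated with 41 participants (the planned total in section 2.3), 20,000 runs per scenario, and two independent variables. With one or both variables log-normal (log SD 1 or 1.5), Pearson rejected in 4.9% to 5.4% of runs and Spearman in 5.0% to 5.1%. There is no material inflation.

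**3. Does skewness cost power?**

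This was simulated with n = 39 (the section 2.3 figure before the dropout allowance), a log-normal marker, a normal exercise measure and a log-scale correlation of 0.45. The skew and the correlation are assumptions; the documents give neither.

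| Log SD of marker | Pearson, raw scale | Spearman | Pearson, log scale |
|---|---|---|---|
| near 0 (no skew) | 84% | 79% | 84% |
| 0.5 | 79% | 78% | 83% |
| 1 | 70% | 80% | 84% |

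Repeated runs moved these figures by one or two percentage points. Raw Pearson matches or beats Spearman up to moderate skew and falls behind by about 10 points at strong skew. Where the log scale is the right one, log-scale Pearson is as good as or better than both throughout.

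**The case against.** The strongest case against the point is that these correlations are peripheral. They are neither a primary nor a secondary outcome. The Discussion uses the language of exploration and calls the results preliminary and in need of confirmation. The Introduction frames mechanism first as the effect of ubiquinol on blood and autonomic markers, which is a randomised comparison. The list of pairs, transformations and false-discovery control are often left to an analysis plan that is not shown here. This stands, and it limits the point to a minor one. It does not remove it, because the article does not stay silent on method: it names the tests and the threshold, and better choices cost almost nothing.

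A reader might infer four stronger things that the documents do not support.

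- *That the plan would produce about 27 false positives at each visit, or about 80 over three blood-sampling visits (3 × 26.6 = 79.8).* No all-by-all matrix is announced, and the Discussion places the exploration at high altitude.
- *That Pearson is invalid for skewed markers.* The false-positive rate holds. The loss is power, and only under strong skew, which the documents do not establish for any marker.
- *That a recorded item such as sex shows Spearman being misused.* No correlation with sex is planned, and for two binary variables Spearman equals the phi coefficient. The difficulty arises only with three or more unordered categories.
- *That the trial's mechanistic conclusion rests on these correlations alone.* The randomised comparison of the markers also bears on mechanism.

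**Conclusion.** The point holds as a minor one. Section 2.11.2 is inconsistent in expecting non-normal continuous variables while fixing Pearson for all of them. Its term for the variables that receive Spearman is too broad. It applies a 0.05 threshold to correlations without naming any error control.

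If every null is true, expected false positives run from about 1 (19 pairs) to about 13 (266 pairs, the set nearest the stated aim). The figure of about 27 (532 pairs) is an upper end that requires all 38 laboratory measures. The cost of raw Pearson is about 10 percentage points of power at log SD 1 and essentially nil against Spearman at log SD 0.5. Both figures assume n = 39 and a log-scale correlation of 0.45. No primary or secondary conclusion depends on this.

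**What to change.** Amend a few lines of section 2.11.2:

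1. For markers that fail the Shapiro–Wilk check already planned, use Spearman, or Pearson after log transformation.
2. Replace categorical by ordinal in the Spearman rule, so that it covers the graded symptom scores. For any nominal variable, use group comparisons or Fisher's exact test.
3. Report the number of correlations tested, present them as hypothesis-generating, and give Benjamini-Hochberg adjusted values beside the unadjusted ones.

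No new data are needed. The cost is that fewer correlations will be called significant. The primary and secondary analyses do not change.

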### Sample size

2.3.

The G-power tool (version 3.1.9.2, Germany, 2017) was used to calculate the sample size by prior power analysis and to estimate all statistically significant results. The *α* error probability was set at 0.05, and the power (1 − *β*) was set at 0.9. With a correlation among repeated measures of 0.5, a sample size of 39 was determined to be necessary to assess the effects of ubiquinol. A sample size of 36 within two groups (ubiquinol group and placebo group) and within-between interactions were calculated with a nonsphericity correction (*ε*) of 1. Considering a 5% dropout rate, based on a sample size of 39, 41 participants would be required finally.

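### Section 2.11.2 takes up the age question through age subgroups of about 40 participants and lists no treatment-by-age term; if the listed comparisons are repeated within age groups, they cannot show whether the effect differs by age

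*Protocol article*

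**What the plan says.** The age analysis has one clause in section 2.11.2 (Statistical considerations): "subgroups will be defined by age for analysis since it is known that ubiquinol levels decrease with age". No cut-point, number of groups or test is given for it.

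The same paragraph lists the model: "Treatment, altitude, and the treatment multiplied by altitude interaction will be considered independent variables under mixed models". The one interaction named is with altitude; neither age nor treatment by age appears. The between-group comparison named is ubiquinol against placebo at each altitude, and a general rule follows: "Two-sided tests with *p*-values less than 0.05 will be considered statistically significant".

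Section 2.3 (Sample size) arrives at 41 participants, and section 2.4.1 allocates them 1:1. The limitations paragraph of section 3 (Discussion) calls the sample small, says that "it is troublesome to implement hierarchical analysis", and describes the results as preliminary. Age is already collected (Table 1 and section 2.11.1).

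**The concern.** The reason given for the age analysis is effect modification: ubiquinol falls with age, so supplementation may help some ages more than others. The matching null hypothesis is that the treatment effect is the same at every age. A ubiquinol-placebo test inside one age group has a different null, that there is no effect in that group. Two such tests can disagree by chance when the true effects are identical, and one significant group beside one non-significant group is easily read as an age pattern.

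A second, separate loss comes from the grouping. Age in years is on file, and cutting it into groups discards information that a continuous term would use.

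What is at stake is a supplementary conclusion, for instance that ubiquinol helps only older or only younger travellers. The primary treatment comparison is not affected.

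**Working it through.** **Number available.** The plan inflates 39 for 5% dropout: 39 × 1.05 = 40.95, giving its 41 (dividing, 39/0.95 = 41.05, would give 42). I take 40 evaluable, 20 per arm. Two equal age halves then hold about 10 per arm each.

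**Assumptions not in the document.** Two age groups split at the median; one outcome at one time point; effects in SD units, since section 2.3 states no effect size; two-sided 0.05 as in section 2.11.2.

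**Step 1: power within one half.** Two-sample t-test, 18 df, noncentrality d/√(1/10 + 1/10) = d/0.447. For d = 0.8 this is 1.79 and power is 0.395.

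**Step 2: disagreement when the effect is the same at every age.** With power p in each independent half, the chance that exactly one half is significant is 2p(1 − p). For d = 0.8: 2 × 0.395 × 0.605 = 0.478.

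| True uniform effect (SD) | Power, 20 v 20 | Power per half, 10 v 10 | Exactly one half significant |
|---|---|---|---|
| 0 | 5% | 5% | 9.5% |
| 0.5 | 34% | 19% | 30% |
| 0.8 | 69% | 40% | 48% |
| 0.91 | 80% | 49% | 50% |
| 1.0 | 87% | 56% | 49% |
| 1.05 | 90% | 60% | 48% |

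With three age groups of about 7 per arm at 1.05 SD, power per group is 0.441. The groups then disagree in 1 − 0.441³ − 0.559³ = 74% of trials.

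**Step 3: the direct test under the same conditions.** In simulation with a uniform effect, a treatment-by-age test is significant in about 5% of trials (5.3% with continuous age, 4.9% with a median split). The excess in step 2 therefore comes from comparing p-values across groups, not from grouping as such.

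**Step 4: the cost of grouping.** Simulated power of the interaction test (n = 40, normally distributed age, slope in SD of outcome per SD of age):

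| Slope | Continuous age | Median split |
|---|---|---|
| 0.3 | 14% | 12% |
| 0.5 | 30% | 21% |
| 0.8 | 63% | 43% |
| 1.0 | 81% | 59% |

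For scale, the two halves of a normal distribution have means 2 × √(2/π) = 1.60 SD apart. A slope of 0.8 therefore means that the average effects in the halves differ by 0.8 × 1.60 = 1.28 SD, which is a very large interaction.

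**Step 5: what the sample can support.** A median-split interaction has standard error √(4/10) = 0.632 SD on 36 df. It needs a difference between halves of about 1.82 SD for 80% power and 2.11 SD for 90%.

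**The case against.** - **The within-group test is inferred.** The clause says only that subgroups will be formed. An interaction test could sit in the full protocol or an analysis plan that is not shown, and the listed terms may describe only the main model. This stands, so the step 2 figures are conditional on the natural reading. What is on the page is the choice to split age and a model whose one interaction is with altitude.
- **A reader might infer that a false age pattern is likely.** The documents do not support that as a general statement. The rate is near one half only if a uniform effect of about 0.8 to 1.05 SD exists; it is 30% at 0.5 SD and 9.5% with no effect. Nor does the article say that significance in one group only would be read as an age effect.
- **A reader might infer that the subgroup approach is why a real age pattern would be missed.** That is mainly a matter of about 40 participants. Step 4 shows low power for moderate slopes with either method, so the change relieves the problem only in part.
- **A reader might infer that the Discussion contradicts section 2.11.2.** The phrase "it is troublesome to implement hierarchical analysis" is too loose for that. The analysis named may be stratified or multilevel, and calling it troublesome does not withdraw it. It is better read as a disclosed small-sample limitation.
- **Age is neither a primary nor a secondary question.** True, and this limits the weight of the point without removing it.

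**Conclusion.** The point holds in a limited form. Section 2.11.2 gives an effect-modification reason for the age analysis, chooses age subgroups as the method, and lists no treatment-by-age term. If the listed comparisons are repeated within age groups, their p-values cannot show whether the effect differs by age. With a uniform true effect, exactly one of two halves is significant in 30% of trials at 0.5 SD and 48 to 50% at 0.8 to 1.05 SD, where an interaction test gives about 5%. Grouping age costs a further 9 to 22 percentage points of interaction power at slopes of 0.5 to 1.0 SD per SD of age.

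These sizes rest on 40 evaluable participants, a median split, a single time point and, in step 4, normally distributed age. They do not show that the trial will report a false age pattern, and the better method does not make the sample adequate for moderate age effects. The change is worth making because it is cheap and puts the analysis in line with its stated reason.

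**What to change.** In section 2.11.2, replace the age subgroups with a single treatment-by-age term, with age in years as a continuous variable and its main effect alongside. Report the estimated treatment effect with a 95% CI at chosen ages, for example the lower and upper age quartiles. State that no claim will rest on p-values within age groups. Label the analysis exploratory, in keeping with the small-sample limitation in section 3, and say there that power for moderate age effects is low.

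The cost is a sentence or two of wording and one additional model. No new data are needed, because age is already recorded. The downside is that the effect is assumed to change linearly with age.
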